### Randomization and blinding

Participants will be randomly allocated in a 1:1 ratio to either the intervention or comparison arm. The randomization sequence will be prepared by the data manager (using a computer programme) and allocation will be done by a trial manager. The fieldworkers will phone the trial manager when an individual is ready to be allocated, and the trial manager will inform the fieldworker about the participant’s allocation based on the randomization sequence. The fieldworker will then notify the participant about his/her allocation and associated activities. Investigators will be blind to the sequence generation. The trial manager will have no direct contact with participants, and all allocations will be concealed until the individual is assigned to a study arm. To reduce potential performance bias, allocations will only occur after the first counselling session has been completed. Fieldworkers will conduct the baseline and follow-up assessments, and trained counsellors will deliver the intervention. Fieldworkers conducting the follow-up assessments will be blinded to the randomization arm. Counsellors delivering the intervention and fieldworkers (serving as outcome assessors) will function independently of each other. Counsellors will not conduct any assessments, ensuring that these assessments remain independent from the counselling sessions.

### Interventions

Irrespective of study arm, the interventions will be delivered in a face-to-face format by trained and experienced health counsellors. These counsellors are increasingly being used in health and community settings in South Africa to deliver structured psychosocial interventions and are part of the National Department of Health’s plans to scale up the provision of mental health counselling through task-sharing structured interventions. We have successfully used these counsellors to deliver other psychosocial interventions and have shown that patients prefer lay counsellors to whom they can relate rather than other health workers [36, 37]. See Table 1 for a detailed description of the ASPIRE intervention package.

**Table 1 Tab1:** Components of the ASPIRE intervention package

Theoretical framework (intervention)	Lazarus and Folkman’s coping theory (Lazarus and Folkman, 1984) informs the problem-solving therapy (PST) approach: problem-solving for problems that can be solved and emotion-focused coping for problems that can’t be solved
**Delivering agents**	• Training in generic counselling skills and 2–5 years of counselling experience
**Structure of intervention package**	Four sessions of blended multi-component counselling intervention, to be delivered weekly. Participants have a 6-week window to complete all sessions before timing out of the intervention.
**Structure of sessions**	
***Session #1*** (participants in both arms receive this)	• Conduct screening/assessment of mental health • Provide feedback on results of screening/assessment • Increase knowledge of how depression and/or alcohol use impacts on adolescents • MI to build rapport and develop readiness to change (for alcohol) • Behavioral activation for strategies to address symptoms of depression
***Session #2*** (intervention arm only)	• Patient check-in using MI • Build the rationale for PST o Explain the structure and rationale for PST o Establish positive problem orientation • Teach the steps of PST • First problem-solving exercise with counsellor and homework
***Session #3*** (intervention arm only)	• Patient check-in using MI • Review practice exercises from session 2 and discuss challenges • *Coping with negative thoughts*: explain how to cope with problems that are not important • Second problem-solving exercise with counsellor and an exercise • *Emotional regulation* • Explain how to cope with “big” feelings such as anger • Practice emotional regulation techniques • Third problem-solving exercise with counsellor and homework
***Session #4*** (intervention arm only)	• Patient check-in using MI • Review practice exercises from session 3 and discuss challenges • *Advance process of acceptance*: teach how to deal with problems that are important and cannot be solved • Fourth problem-solving exercise with counsellor and recap • *Bringing it all together*
**ASPIRE training**	
**Structure and format of training**	• Forty hours of formal training (the equivalent of five working days) • Mixture of didactic teaching and experiential group activities including skills rehearsal exercises and role plays • Counselling proficiency assessed during role plays using a competency checklist
**Training content**	• Understanding common mental disorders (CMDs) • Principles of counselling (including confidentiality) • Screening participants for hazardous/harmful alcohol use and depression • Delivery of the blended multi-component counselling intervention • Ethics: recognizing and managing distressed participants and referral for additional care
**Characteristics of supervisor**	• Psychological counsellor, registered with the HPCSA • Five years previous counselling experience in cognitive-behavioral therapy-based brief interventions • Three years previous experience in delivering MI-PST and training healthcare workers • Conduct guided by the professional standards and ethics–Professional Board for Psychology and the HPCSA
**Structure of supervision and debriefing**	• In-person or telephonic individual supervision and debriefing conducted once a week • Telephonic supervision and debriefing used during community unrest, gang violence • Brief communication via text or WhatsApp messaging to address challenges in real-time in between weekly scheduled supervision and debriefing sessions • Supervision and debriefing of up to an hour per session and structured as follows: o Debriefing: brief check-in, followed by reflection on recent experiences at work and/or home, how these experiences were dealt with emotionally and practically (coping) and identifying opportunities for growth o Clinical supervision: counsellors present new cases and/or discuss patient progress including feedback, suggestions or recommendations by supervisor where needed in addition to reviewing counselling session notes o Addressing challenges: discuss logistical and counselling delivery challenges, and brainstorm solutions o Counselling fidelity feedback: provide counsellors with structured feedback on their counselling proficiency using a counselling fidelity checklist (audio tapes of counselling sessions assessed prior to supervision by supervisor). Brief skills rehearsal exercises or role playing to improve and solidify counselling aspects with average to low scores on the fidelity checklist.
**Supervisor training and support**	• Trained to use a structured approach to supervision • Weekly in-person or telephonic supervision provided by a psychologist to assess adherence to the supervision approach and discuss ways of overcoming any logistical and systemic challenges to provision of supervision and debriefing • Weekly in-person or telephonic debriefing provided by a psychologist, including reflecting on recent experiences at work and/or home, how these experiences were dealt with emotionally and practically (coping) and identifying opportunities for growth

#### Comparison arm: session 1 and referral to care

Participants assigned to this arm will have received a single counselling session (~ 1 h in duration) prior to allocation. This is session one of the ASPIRE intervention, and the content and delivery of this session will be identical to that received by participants assigned to the intervention condition. The session includes screening for heavy alcohol use and depression, feedback about the screening results and levels of risk, psycho-education about how alcohol or feelings of depression can affect young people, and (depending on their primary condition), motivational interviewing to enhance motivation to reduce alcohol use or behavioral activation to address symptoms of depression. The session will conclude with the participant setting personal goals and developing a plan for change, guided by the counsellor. Participants will also be given referrals to usual care providers for further follow-up if required.

#### Intervention arm (ASPIRE intervention)

Participants assigned to this condition will receive session one as described above, plus an additional three sessions of  a blended multi-component counselling intervention that has shown efficacy in other studies [8]. The goals of this intervention are to motivate participants to make changes to their risk behaviors and strengthen their problem-solving skills to help them cope better with stress and life problems that are risk factors for common mental disorders. The intervention is largely based on Lazarus and Folkman’s [38] coping theory, teaches problem-focused coping skills for mutable problems and emotion-focused coping strategies (acceptance and seeking support) for immutable problems. In this approach, heavy alcohol use is viewed as a form of problem avoidance (maladaptive emotion-focused coping) and depression, a response to maladaptive emotion-focused coping [38]. See Fig. 2 for a conceptual model of the ASPIRE intervention. Each session functions iteratively to build readiness to change and adaptive problem-solving and coping skills. All sessions have a motivational component, a psycho-education component (in which participants are taught problem-solving skills and how to apply them) and include an opportunity to apply newly learned skills through exercises and homework. More specifically, participants are taught steps for addressing problems that are important and can be solved; strategies for dealing with negative and intrusive worries that are unimportant; and steps for coping with problems that are important but cannot be solved [8, 39]. Participants will also be taught techniques for managing uncomfortable emotions. A patient handbook, summarizing the content of the counselling sessions and containing worksheets that participants use to practice the problem-solving method, is used to guide counselling. The handbook is available in English, Afrikaans, or isiXhosa (the three official languages of the Western Cape). From enrolment, participants in the intervention arm will have 6 weeks to receive all four sessions of the intervention. Each counselling session should be spaced at least 5 days apart, with the first session occurring immediately after the baseline assessment. The duration of each counselling session is approximately 45–60 min.

**Fig. 2 Fig2:**
[figure not shown]
Conceptual model of the ASPIRE intervention

### Counsellor training and supervision

ASPIRE counsellors selected to be trained will already have basic counselling training. For this study, they will receive an additional 40 h of training in understanding common mental disorders, screening for hazardous/harmful alcohol use and depression, principles of basic counselling (including confidentiality), motivational interviewing and problem-solving therapy (with proficiency testing through role-playing and case examples), providing referrals, and responding to distressed participants. Prior to the start of training, counsellors will complete an assessment of their knowledge, attitudes, beliefs, and practices around counselling for common mental disorders, and these will be assessed after completion of training to evaluate the impact of training.

Following training and continuing throughout the implementation of the interventions, counsellors will participate in regular face-to-face and virtual supervision and debriefing that will be conducted by a registered psychological counsellor (see Table 1 for further details). The content of supervision will include review of the logistics of implementing the intervention (to troubleshoot any barriers), a review of participants’ progress and debriefing about challenges, feedback from fidelity checks about the quality of intervention delivery, and how it can be improved. Counsellors will take notes after each counselling session, which will be reviewed during supervision by the counsellor supervisor. Supervision will also be an opportunity for on-going booster training, as and when required. If quality assurance activities indicate that some counsellors require more training in the intervention, this will be provided. The number of hours spent on training, supervision, and debriefing per individual counsellor will be recorded in a training and supervision log. The counsellor supervisor in turn will be supervised by a psychologist. Supervision sessions will be recorded for fidelity and reviewed, with feedback provided to improve the quality of supervision. We have used this model of supervision successfully in our previous work [29].

### Counsellor competency and monitoring

To assess and monitor counsellor competency in both arms, we will audio-tape counselling sessions with consent from participants. For the comparison arm, counsellors’ competency in delivering session 1 will be assessed. For participants in the intervention arm, one session will be randomly selected from the total number of completed sessions to be assessed for counsellor competency. Both treatment-specific competencies and core therapeutic competencies will be assessed by the counselling supervisor.

For treatment-specific competencies (often referred to as fidelity), an intervention delivery checklist will be used which includes items pertaining to (1) use of a motivational interviewing counselling style; (2) dosage (duration of counselling session and amount of time spent on non-intervention related topics); and (3) whether the objectives of the intervention session were addressed adequately. For this project, we will rate these competencies using Likert scales, with 1 being “not at all present” and 5 being “present most of the time. For core competencies, a South African version of the ENhancing Assessment of Common Therapeutic Factors [40] will be used to measure core therapeutic competencies and skills that are thought to be required for a counsellor to adequately deliver any evidence-based intervention.

### Feasibility outcomes

The schedule of data collection is shown in (Fig. 3) the SPIRIT Figure. The primary objective of this study is to evaluate the feasibility and acceptability of the ASPIRE intervention, and the trial procedures required for the implementation of a future effectiveness trial. In line with recommendations for the reporting of pilot studies [41], we have identified several quantitative and qualitative indicators of feasibility and acceptability that will be used to guide decisions about what procedures to carry through to the full trial and when modifications to procedures or intervention content and delivery should be made. These include (1) feasibility of recruitment; (2) appropriateness of data collection processes and outcome measures; (3) retention in the ASPIRE intervention; (4) counsellor competency; (5) feasibility of randomization and blinding; (6) presence of adverse advents; and (7) acceptability of the ASPIRE intervention and study procedures. Table 2 describes these indicators, how they will be evaluated and pre-determined progression criteria (where applicable). Progression criteria have been set to facilitate the interpretation of results and to inform whether to proceed to a definitive trial after the feasibility study.

**Fig. 3 Fig3:**
[figure not shown]
Standard Protocol Items: Recommendations for Clinical Trials (SPIRIT) Figure–schedule of data collection

**Table 2 Tab2:** Overview of feasibility and acceptability outcomes and progression criteria

Outcome	Evaluation	Progression criteria to controlled trial^**a**^
**Feasibility of recruitment**	• Numbers screened, number of eligible participants, number invited to participate, consent rates (for parents and adolescents), refusal rates and reasons for refusal	• Enrolment of at least 5 participants per week
**Appropriateness of data collection processes and outcome measures**	• Number of missing items and follow-up rates	• Less than 15% missing items for each measure
**Retention in the ASPIRE intervention**	• Number of participants who completed at least three sessions	• At least 70% of participants complete the counselling programme
**Counsellor competencies in delivering the ASPIRE intervention**	• Scores on a counsellor competency checklist	• 75% competency
**Feasibility of randomization**	• Number of consent/assent • Number of refusals to be randomized	• At least 80% participation
**Feasibility of blinding**	• Field staff perceived contamination	• Very minimal perceived contamination (less than 5%)
**Presence of adverse events**	• Number of study-related adverse events reported	• Less than 10% of participants reporting severe adverse events related to the study
**Acceptability of the ASPIRE intervention**	• Qualitative interviews with participants and counsellors following the feasibility trial	• Not applicable
	• Scores on the Child Evaluation Inventory (CEI) used to assess participants’ satisfaction with the intervention and how it was delivered	• More than 80% of participants scored a total of 60 or more on the CEI
**Acceptability of the study design and procedures**	• Participants will be asked to rate the acceptability of the study procedures, including (i) screening, (ii) consent, (iii) assessment (length, type of questions, mode of administration), (iv) randomization, (v) referrals (and uptake of referrals), and (vi) tracking for follow-up assessments. They will rate these items on a 5-point scale (from 1 = not at all acceptable to 5 = very acceptable).	• More than 80% of participants score 3 or more for each rating

^a^If one or more criteria are not met revisions should be considered before proceeding to a definitive trial

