### Data analysis

The quantitative outcomes of interest (see Table 2) will be summarized descriptively using appropriate summary statistics (mean and standard deviation for continuous outcomes and numbers and proportions for categorical outcomes) and presented graphically over time for both study arms.

We will explore clinical outcomes. In these exploratory analyses, we will calculate means and confidence intervals of clinical outcomes (both within- and between-study groups) and determine which outcomes are most sensitive to change. We will evaluate the parameters required to inform the sample size calculation for a future main trial. We will also assess change in clinical outcomes using an intention-to-treat analysis. Outcomes will be compared between intervention and control groups using linear regression models, adjusting for the baseline score of the given outcome. We will create separate models for alcohol and depression and only include participants who screen at risk at baseline. The two primary outcomes will be ascertained at three time-points for each participant. This repeated measure feature will be used to estimate the intervention effects and 95% confidence intervals for the two primary outcomes at 6 weeks and 3 months for the contrast between the intervention and comparison condition.

Qualitative data will be coded with NVivo and analyzed using the framework approach [56]. Transcripts of interviews will be read for emergent themes and then coded. Coding and analysis will continue iteratively. Two project staff will code the transcripts; they will meet after the first five transcripts, and thereafter after every 10 transcripts, to compare notes. Cohen’s Kappa will be used to measure inter-coder agreement. Following the Consolidated Criteria for Reporting Qualitative Studies (COREQ), we will document the process according to the 32-item checklist [57].

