#### Anticipated risks

The main risk associated with this study is the potential mental discomfort that may arise from material covered in the assessments or intervention sessions. This will be minimized by using experienced and well-trained fieldworkers and counsellors and the option of referral to mental health and substance use services in both arms. Staff will be trained on how to identify distressed participants who may be at risk of harm and will be supported in managing these participants telephonically during the patient contact time, and during regular supervision and debriefing sessions. For participants who are distressed and at risk of harm, we will actively refer and link them to appropriate resources to help them cope and deal with their distress. A further risk shared with other psychotherapy interventions is initial worsening of symptoms and risk of suicide arising from issues uncovered during counselling. To minimize this potential harm, we will train staff to screen all participants who report or display signs of distress for risk of suicide (using the Columbia Suicide Severity rating [58] scale and to provide referrals to specialized mental health services.

All adverse events (AE) and serious adverse events (SAEs) that are reported by the participant or observed by the field workers or counsellors will be recorded. All staff will be trained to follow the Distressed Participant Protocol that provides the process of reporting and supporting/referral in case of any adverse events. All AEs and SAEs will be reported to a local independent Trial Steering Committee (TSC).

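### Table 2 defines the safety outcome by study-related adverse events only, although all events are recorded and the named harms are hard to attribute in this population (minor)

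*Protocol article*

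**What the plan says.** In the protocol article, Table 2 has a row for the presence of adverse events. Its evaluation is "Number of study-related adverse events reported" and its progression criterion is "Less than 10% of participants reporting severe adverse events related to the study". The table footnote says that an unmet criterion should lead to revisions being considered before a definitive trial.

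The Data analysis section ties the summaries to that table: "The quantitative outcomes of interest (see Table 2) will be summarized descriptively using appropriate summary statistics". The same sentence adds graphical presentation over time for both arms.

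The Anticipated risks section is wider. It covers "All adverse events (AE) and serious adverse events (SAEs) that are reported by the participant or observed by the field workers or counsellors", all of which are to be recorded and passed to the independent Trial Steering Committee. The main risk it names is "the potential mental discomfort that may arise from material covered in the assessments or intervention sessions". A further risk is "initial worsening of symptoms and risk of suicide arising from issues uncovered during counselling".

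Under Participants, adolescents enter because they screen at risk on the CES-D-10 (10 or more) and/or at moderate or severe alcohol risk on the ASSIST-Y (5 or more).

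**The concern.** The trial collects every event, but the safety outcome it defines is only the part judged to be caused by the study. Worsening mood or suicidality in an adolescent enrolled for depression risk may come from the counselling, from the assessments, or from the course of the condition itself. A single case seldom shows which. This step is an inference, but it follows from setting the protocol's own list of harms beside its own entry criteria.

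With the same recorded events, the stated result would be larger or smaller depending on how those judgements fall. Planners of the definitive trial would learn how many events were attributed to the study, but not, from the outcome as defined, how many adolescents had a severe or serious event at all.

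**Working it through.** No figure in the plan needs reproducing. The 10% threshold is set without a derivation, and no event rate is given. The check compares the sections and then looks at what the proposed counts can and cannot show.

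**1. Recorded against defined.**
- Recorded (Anticipated risks): all AEs and SAEs, reported or observed, with no filter on cause.
- Defined as outcome (Table 2): study-related events only.
- Summarised (Data analysis): the quantitative outcomes in Table 2.

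The relatedness filter is applied in Table 2, not at data collection.

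**2. What the filter does.** Let A be the number of participants with a severe event of any cause and s the share judged related. The related number is R = A × s. The documents give neither A nor s. Reporting R alone leaves both unknown; reporting A and R gives s = R / A, so the reader can see how much was attributed. R itself, and any criterion based on it, is the same before and after the fix.

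**3. What other measures cover.**
- The CES-D-10 outcome is repeated at 6 weeks and 3 months in both arms without attribution, but is restricted to those scoring 10 or more at baseline.
- The GAD-7 is repeated with no stated restriction, but measures anxiety.
- Suicide-risk screening is triggered; staff are to "screen all participants who report or display signs of distress for risk of suicide". It is not a uniform measurement in all participants.

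The scales cover much of symptom worsening. What remains is discrete events, above all suicide-related ones.

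**4. What an arm contrast can show.** Both arms receive the baseline assessment and an identical session 1 before allocation, and both have the same follow-up assessments. A difference between arms therefore reflects only sessions 2 to 4. Harm from the shared parts can appear only in the overall and related counts, which is why the related subset must stay.

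**5. Unequal contact.** After allocation the comparison arm has 2 scheduled contacts (6 weeks, 3 months). ASPIRE has up to 3 + 2 = 5. If an event is noted with probability p at each contact, independently, the chance of at least one is 1 − (1 − p)^k. With p = 0.02, an assumption:
- comparison: 1 − 0.98² = 4.0%
- ASPIRE: 1 − 0.98⁵ = 9.6%

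At p = 0.01 the figures are 2.0% and 4.9%; at p = 0.05 they are 9.8% and 22.6%. Contact alone can produce an apparent excess. If the display is restricted to the two common visits, k = 2 in both arms and this effect disappears in the model.

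**6. Precision at 50 per arm.** Wilson 95% interval: [p + z²/2n ± z√(p(1 − p)/n + z²/4n²)] / (1 + z²/n), with z = 1.96 and n = 50, for two assumed counts:
- 5/50 = 10%: (0.1384 ± 0.0916) / 1.0768, or 4.3% to 21.4%
- 10/50 = 20%: (0.2384 ± 0.1173) / 1.0768, or 11.2% to 33.0%

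The two intervals overlap widely, so the arm columns can support description only.

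**The case against.** The strongest reply is that Table 2 lists progression indicators, not the whole safety report. The Data analysis section says Table 2 outcomes will be summarised; it does not say that nothing else will be. Full adverse event tables are commonly left to an analysis plan, which is not shown here. A reader might infer that any-cause events will go unreported or escape oversight. The document does not support that: all of them reach the independent committee, which monitors safety. What does not fall to this reply is that Table 2 positively names the related subset as the outcome. A causality procedure in a fuller document would not alter that definition.

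Second, a related-event count suits a table meant to show which study procedures need changing. That stands, and it is why the count and its criterion should be kept.

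Third, a reader might infer that the evaluation cannot supply the criterion's numerator, because one counts events and the other participants with severe events. That is compressed table wording. The Confidentiality section links forms by a unique participant number, so participants can be counted from the same records.

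Fourth, display for both arms is already stated under Data analysis. The by-arm element of the fix only makes it explicit for the event counts; the new element is the any-cause count.

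**Conclusion.** The point holds as a minor one. Table 2 fixes a safety outcome narrower than the data collected, on a judgement that is hard to make for the harms the protocol itself expects. The gap lies in the stated event-based safety result only.

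A reader might go further and conclude that the progression decision is unsound or that the 10% rule should be based on all severe events. The documents do not support this. The rule is advisory, related events are relevant to revising procedures, and any-cause counts would bring in background events. Nor would a comparison of arms settle attribution, given the shared session 1, the extra ASPIRE contacts and the small numbers.

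The effect on the trial's safety result cannot be sized, because neither event rates nor attribution shares are given. The contact and precision figures rest on assumed values and describe the limits of the proposed counts, not the size of the defect. The difficulty of attribution is an inference from the entry criteria and the named harms.

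**What to change.** Replace the Table 2 evaluation for adverse events with: *Number and percentage of participants with any AE, any severe AE and any SAE, regardless of judged relationship, by arm and overall, with events judged study-related as a subset.*

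Keep the advisory 10% related-event criterion. Read the any-cause counts descriptively beside it, with no between-arm test and no new decision rule.

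State two limits with the table: the arm contrast reflects only sessions 2 to 4, and ASPIRE participants have up to three more contacts at which events can be noticed. A second display restricted to the 6-week and 3-month visits is optional, where the date of each report exists.

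The cost is one reworded cell and one descriptive table from events already to be recorded. Severity is already presupposed by the existing criterion, so no new form field is needed, which matters because 67 of the planned 100 participants had been recruited when the trial was paused. The downside is that any-cause counts include background events and are imprecise at about 50 per arm.
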